# Administration of taurolidine-citrate lock solution for prevention of central venous catheter infection in adult neutropenic haematological patients: a randomised, double-blinded, placebo-controlled trial (TAURCAT)

**DOI:** 10.1186/s13063-018-2647-y

**Published:** 2018-05-02

**Keywords:** Catheter-related bloodstream infection, Central venous catheter infection, Antibiotic lock technique, Lock solution, Taurolidine-citrate, Haematological patients, Neutropenia

## Abstract

**Background:**

Catheter-related bloodstream infection (CRBSI) is one of the most frequent complications in patients with cancer who have central venous catheters (CVCs) implanted and is associated with substantial morbidity and mortality. Taurolidine is a non-antibiotic agent with broad-spectrum antimicrobial activity, which has been used as a lock solution to prevent CRBSI in some settings. However, little is known about its usefulness in high-risk adult neutropenic patients with cancer. This prospective randomised clinical trial aims to test the hypothesis that taurolidine-citrate lock solution is more effective than placebo for preventing catheter infection in neutropenic haematological patients.

**Methods:**

This study is a prospective, multicentre, randomised, double-blinded, parallel, superiority, placebo-controlled trial. Patients with haematological cancer who are expected to develop prolonged neutropenia (> 7 days) and who have a non-tunnelled CVC implanted will be randomised to receive prophylactic taurolidine-citrate-heparin solution using a lock technique (study group) or heparin alone (placebo group). The primary endpoint will be bacterial colonisation of the CVC hubs. The secondary endpoints will be the incidence of CRBSI, CVC removal, adverse events, and 30-day case-fatality rate.

**Discussion:**

The lock technique is a preventive strategy that inhibits bacterial colonisation in the catheter hubs, which is the initial step of endoluminal catheter colonisation and the development of infection. Taurolidine is a nontoxic agent that does not develop antibiotic resistance because it acts as an antiseptic rather than an antibiotic. Taurolidine has shown controversial results in the few trials conducted in cancer patients. These studies have important limitations due to the lack of data on adult and/or high-risk neutropenic patients, the type of catheters studied (tunnelled or ports), and the lack of information regarding the intervention (e.g. dwelling of the solution, time, and periodicity of the lock technique). If our hypothesis is proven, the study could provide important solid evidence on the potential usefulness of this preventive procedure in a population at high risk of CRBSI, in whom this complication may significantly impair patient outcome.

**Trial registration:**

ISRCTN, ISRCTN47102251. Registered on 9 September 2015.

**Electronic supplementary material:**

The online version of this article (10.1186/s13063-018-2647-y) contains supplementary material, which is available to authorized users.

## Background

Catheter-related bloodstream infection (CRBSI) is one of the most frequent complications associated with the long-term use of catheters. Patients with cancer usually have central venous catheters (CVC) implanted for an indefinite period for the administration of chemotherapy and other products and medications and are at increased risk of presenting with this complication, especially during the neutropenic phase. CRBSI in patients with cancer is associated with substantial morbidity and mortality, with excess costs and prolonged length of hospital stay [1–3]. Importantly, CRBSI can delay the administration of chemotherapy, which may negatively influence patient outcomes [4].

Gram-positive organisms, mainly coagulase-negative staphylococci (CNS) and *Staphylococcus aureus*, are the leading cause of CRBSI in patients with cancer [1]. However, an increasing number of episodes of CRBSI due to Gram-negative bacilli and fungi have been recently documented in some institutions [5–7]. In addition, an alarming emergence of antimicrobial resistance is being observed among Gram-negative bacteria infecting high-risk patients with malignancies [8, 9]. This is of special concern due to the associated increased mortality of bloodstream infections (BSI) due to resistant organisms in neutropenic cancer patients [10–12].

The most frequent mechanism of infection with long-term, non-tunnelled CVC use is catheter hub contamination during catheter manipulation by health personnel, leading to endoluminal colonisation and infection [13, 14]. Bacterial colonisation of catheter lumens leads to the development of a microbial consortium associated with the catheter surface and embedded in an extracellular matrix, named biofilm, which hinders antibiotic penetration and bacterial eradication [15]. Catheter removal and treatment with systemic antibiotics is the ‘gold standard’ approach for CRBSI [14, 15]. However, in neutropenic cancer patients, the removal of their ‘highly needed’ catheter is not always feasible, even when the diagnosis of catheter infection is established [16]. Therefore, prevention of CRBSI in these high-risk patients is crucial.

The use of lock therapy with different solutions as a method of preventing luminal catheter colonisation is an effective strategy in reducing CRBSI [17]. Lock therapy involves instillation of a solution into the catheter lumen for a variable period of time, depending on the solution at hand [18]. Moreover, the use of lock therapy decreases the incidence of CRBIS in some studies involving patients with cancer [19]. However, significant differences in the definitions of CRBSI exist in the studies performed, as well as in the type of catheters, the solutions used, and the dwelling times. Additionally, almost all studies have been performed in paediatric populations, and the number of high-risk neutropenic patients included in the studies is very small. In fact, national guidelines do not currently support the prophylactic use of lock therapy in patients with cancer, while waiting for higher-quality scientific evidence.

Vancomycin, ethanol, and taurolidine have been the most frequently studied lock solutions in patients with cancer, with very variable results, according to the significant aforementioned differences in the methodology of the studies and the population involved [20–29]. Of note, there is great concern regarding the use of vancomycin as a lock solution, since there is a risk of developing antibiotic resistance. Furthermore, the adverse events observed with the use of ethanol discourage its use as a lock solution. Taurolidine is a non-toxic substance derived from the amino acid taurine, which has anti-adherent, immunomodulatory, antithrombotic, and antitumour properties [30]. Although it is not an antibiotic, it has a wide array of antimicrobial activity against a broad spectrum of microorganisms, including Gram-positive bacteria, Gram-negative bacteria, and fungi. Taurolidine-citrate was found to be effective in two [28, 29] of the three studies involving paediatric patients with cancer, reducing CRBSI rates compared with heparin solutions, but it did not offer any benefit when used in the single adult study performed in patients with non-haematological cancer who had totally implantable venous access ports implanted [31]. The scarce and heterogeneous data obtained from these studies do not draw any solid conclusion. Moreover, almost all reported studies involved paediatric patients, and the devices studied in all of these trials were tunnelled catheters or ports.

This prospective, multicentre, randomised, double-blinded, placebo-controlled trial aims to test the hypothesis that lock solution with taurolidine-citrate-heparin is more effective than placebo for preventing CVC catheter infection in high-risk neutropenic haematological patients.

### Objectives of the study

This study aims to determine whether taurolidine-citrate-heparin lock solution is more effective than heparin alone for the prevention of CVC infection in neutropenic haematological patients.

### Primary endpoint

Bacterial colonisation of the CVC hubs.

### Secondary endpoints

Incidence of CRBSI, CVC removal, adverse reactions, and 30-day case-fatality rate.

## Methods

### Study design

This study is a prospective, multicentre, randomised, double-blinded, parallel, superiority, placebo-controlled trial (1:1). Patients will be randomised after completion of chemotherapy. Patients who were expected to develop prolonged (> 7 days) neutropenia will be randomised to receive a prophylactic solution of taurolidine-citrate-heparin using the lock technique (study group) or a solution with heparin alone using the same technique (placebo group). The study will be conducted in accordance with the Standard Protocol Items: Recommendations for Interventional Trials (SPIRIT) recommendations [32], Additional file 1.

### Study population

This study includes adult patients with haematological malignancies admitted to the haematology wards who are receiving chemotherapy, who are expected to develop prolonged neutropenia (> 7 days), and who have a non-tunnelled CVC implanted.

### Setting

The study will be conducted in Institut Català d’Oncologia L’Hospitalet (ICO Hospitalet), a 100-bed capacity hospital for adult patients, a referral cancer centre for a population of one million people. University Hospital of Bellvitge (HUB), an 800-bed-capacity tertiary hospital for adult patients. Both hospitals are located in the same health complex and are part of the Institute of Biomedical Research of Bellvitge (IDIBELL). Hospital Universitario Virgen del Rocío (HUVR) is a 1700-bed capacity hospital that caters to half a million inhabitants in the province of Seville.

### Selection of cases and recruitment

Patients admitted in the haematology wards of the two participating centres receiving myeloablative chemotherapy and who are expected to develop prolonged neutropenia (> 7 days) will be followed up daily by the attending physicians and by a research nurse specifically commissioned to carry out this study. Screening swabs from the catheter hubs and the catheter insertion site will be collected previous to randomisation by the usual nursing personnel; then, the catheter samples will be sent to the microbiology laboratory in order to identify patients with positive cultures (exclusion criteria). Patients with negative screening cultures will be followed up daily by the research nurse in charge and/or the investigators of the study, to assess whether they meet all the inclusion criteria and none of the exclusion criteria. A blood test will be performed every 2–3 days according to the protocols of each centre to document the development of neutropenia. Patients with neutropenia who met the inclusion criteria will be asked to sign the informed consent. The research nurse in charge and/or the investigators of the study will explain the study to the potential participants and ask them to sign the informed consent.

### Inclusion criteria

Patients aged 18 years or older who are admitted to the hospital because of leukaemia, lymphoma or to undergo haematopoietic stem-cell transplantation (HSCT)Carriers of multiple-lumen, non-tunnelled CVCs, including peripherally inserted central catheters (PICCs)Patients who are expected to develop neutropenia (< 500 neutrophils/μL) lasting more than 7 days

A patient could be included twice if two independent periods of neutropenia occur with at least 1 month interval between them. This interval will be calculated from the final visit (30 days from the end of the intervention) to the new inclusion. In this cases, patients will be randomised again.

### Exclusion criteria

Patients with a (non-flexible) semi-rigid or tunnelled CVC or totally implantable venous access portsPatients who have been found to have a positive culture of the hubs or the insertion site of the CVC based on the results of the baseline screening culturesPatients in whom the CVC is indispensable for the use of continuous infusion medicationPatients receiving systemic antibiotic treatment ≥ 48 h prior to study entryPatients with an active infection

### Randomisation

In this randomised, double-blinded study, neither the patient nor any of the health staff will know which product is assigned to each patient.

A unique list of coded numbers containing the randomised solutions will be generated in the Clinical Research Unit. The randomisation will be performed in each block and stratified. The stratum will contain three groups: patients with leukaemia, patients undergoing an autologous transplantation, and patients undergoing an allogeneic transplantation. The random number generator of SAS version 9.2 will generate the three lists. Once generated, the list will be kept in the pharmacy file, in the pharmacy department of ICO Hospitalet with restricted access to the blinded personnel involved in the trial. When a patient from any of the two participating centres meets the inclusion criteria and signs the informed consent, an email with the recruitment sheet of the patient will be sent to the pharmacy department of ICO Hospitalet, where the randomisation will take place, by the investigator from the pharmacy department in charge of the study. The assignment will be made sequentially, and each patient will be assigned a randomisation number.

The taurolidine-citrate-heparin and the heparin-placebo solutions will be prepared in each pharmacy department, and they will be dispensed in 2.5-mL syringes identified with the name of the drug, defined as heparin/taurolidine-citrate, to maintain the blinding. Citrate is an anticoagulant substance without antimicrobial activity, which accompanies taurolidine as an antiaggregant agent. Both lock solutions are colourless and odourless, which makes further masking unnecessary. The blind will be open before the statistical analysis, but only when the trial has concluded and the definitive data will be registered in the database. Only in cases with suspected serious adverse events will the blinding be open.

### Intervention

Once the randomisation has been performed, a syringe containing 2.5 mL of the assigned lock solution (taurolidine 2%-citrate 4%-heparin 500 UI/mL, or heparin 1% alone at a dose of 1000 UI/mL) will be injected, by usual haematology ward nurses, through each catheter lumen three times a week, approximately every 48-72 h. The solution will be allowed to dwell for approximately 2 h. In all cases, the solution will be aspirated with a syringe and discarded. Before the lock technique, cultures of the hubs and the CVC insertion site will be taken in order to assess the bacterial colonisation of these sites. The research nurse in charge of the study will supervise all the proceedings related with the intervention. Also, the nurse in charge will periodically provide a report to the principal investigator of the study, informing whether the interventions have been performed properly.

### Catheter management

Multilumen, non-tunnelled CVCs will be inserted into the vein by a specifically trained staff, under the standard precautions. At the time of the catheter placement, the insertion site will be disinfected with 2% chlorhexidine in an alcohol base and then covered with a transparent dressing, except in patients with allergy to this type of dressing, in whom sterile gauze will be used. Also, when there is any sign of inflammation at the insertion site, the dressing will be replaced by a chlorhexidine-impregnated dressing. The care of the CVCs will include the replacement of the dressings every 6–10 days, or before if necessary. Before any manipulation, the catheter hubs will be disinfected using an external clean with 70° alcohol. If the catheter is sealed, the hubs will be disinfected every 6–10 days. If any of the catheters lumens become sluggish or occluded, flushing with urokinase will be performed. Any change of these procedures will be recorded in the database. The manipulations of the CVCs will be carried out under maximum barrier measures.

### Follow-up criteria and participant timeline

Patients will continue to receive intervention until one of following events occurs:Positivity of any of the cultures taken from the CVC hubsRecovery of neutropenia: > 500 neutrophils/μLRemoval of the catheter for any causeEpisode of CRBSINeed to use the CVC for the administration of a medication in continuous infusion that cannot be stopped for any reasonDischarge from the haematology ward for any reason, despite not having recovered from the neutropeniaDeath

Once the patient concludes the study for any of the previous events, a 30-day follow-up will take place to assess possible complications until that date. The intervention will be stopped in patients in whom significant colonisation of a CVC hub is detected, but they will continue to be followed-up to check whether they develop CRBSI. Whenever the catheter is removed on suspicion of infection, the hubs and tip of the catheter will be sent for microbiological culture.

A patient will be considered to have discontinued the study when the patient withdraws the informed consent, dies, or is lost to follow-up. The trial will be considered finished when all the recruited participants have completed the 30-day follow-up period. Figure 1 shows the participant timeline of the study.

**Fig. 1 Fig1:**
[figure not shown]
Participant timeline of the study

### Interruption criteria

Withdrawal of consentViolation of maskingViolation of the inclusion/exclusion criteriaSerious adverse reaction

In accordance with the current revision of the Declaration of Helsinki and the applicable regulations, a patient has the right to withdraw from the study at any time and for any reason, without this causing any harm to the medical care by their physician. The withdrawal of full consent from a study means that the patient does not wish to continue participating in the study. Any patient withdrawing their consent will be removed from the treatment and/or the study observations immediately after the date the patient requests it.

### Data collection

The following data will be collected: sex, age, type of underlying disease, other comorbidities, date of hospital admission, HSCT, type and date of HSCT, immunosuppressive therapy, concomitant medication, duration of neutropenia, type of CVC, days from CVC insertion to inclusion in the study, use of prophylactic antibiotics or antifungal agents, systemic antibiotic therapy, number of catheter locks per episode, results of the cultures of the hubs and CVC insertion site, any episodes of infection, episodes of CRBSI, the need for CVC removal and reason, development of complications, adverse reactions, overall case-fatality rate, CRBSI attributable case-fatality rate, and date of discharge.

### Definitions

Significant colonisation of any catheter hub will be defined as the presence of any microbial growth in the qualitative culture of the swabs. CRBSI will be defined as the detection of growth of bacteria or fungi in at least one blood culture obtained from a peripheral vein, associated with clinical signs and symptoms of infection (e.g. fever, chills, and/or hypotension), and no apparent source for BSI other than the CVC. In the case of common skin-colonising microorganisms, such as CNS, two positive sets of blood cultures will be necessary to make the diagnosis of CRBSI. CRBSI attributed to luminal colonisation will be defined as the isolation of identical organisms from the catheter hub and from cultures of separate percutaneously drawn blood specimens; the organism’s identity will be proven by molecular typing for patients with BSI due to CNS. Overall, the 30-day case-fatality rate will be defined as death by any cause within the 30 days following the end of the intervention.

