### Study outcomes and endpoint assessment

#### Primary endpoint

For the assessment of the primary endpoint (bacterial colonisation rate of the CVC hubs), swabs of the inner surfaces of the catheter hubs will be obtained by the nursing personnel before randomisation and three times weekly (approximately every 48-72 h) thereafter for culture, until the end of the intervention. All swabs are made of viscose, and only the swab of the catheter insertion site has a transport media (Stuart media). One swab is used for each lumen The cultures of the collected swabs will be processed in the microbiology department. The results of the cultures will be reviewed by the participating investigators and will be written down in the data collection form and in the specific database.

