#### Secondary endpoints

The assessment of the secondary endpoints will be performed as follows:Incidence of CRBSI: swabs of the insertion site and catheter hubs as well as blood cultures (at least one from a peripheral vein) will be obtained when CRBSI is suspected. In the case of catheter removal, two 5-cm segments, a proximal subcutaneous segment and the tip, will be sampled using the sterile technique for culture. The incidence of CRBSI and the CRBSI attributed to luminal colonisation will be calculated for each group. The differential time to positivity will not be used to diagnose CRBSI. The development of CRBSI will be assessed during intervention and up to 30 days after the last intervention. The rate of CRBSI will be presented as the number of episodes of CRBSI per 1000 admission daysCVC removal: whenever it is necessary to remove the CVC because of occlusion, thrombosis, dislodgement or suspicion and/or documentation of infection, the tip is going to be sent for culture to the microbiology department, and the reasons for removal will be annotated in the data collection form and the database by the participating investigators. The need for CVC removal will be assessed during intervention and up to 30 days after the last interventionAdverse reactions: any adverse reaction potentially associated with the administration of the lock solution will be annotated in the data collection form and the database by the participating investigators. Adverse events will be identified and classified according to the severity and the potential relationship with the lock solution. They will be assessed during the interventionOverall (30-day) case-fatality rate: all patients included in the study will be followed up for a total of 30 days after the end of the intervention by the participating investigators. Death by any cause will be annotated in the data collection form and the database

The research nurse in charge of the study will visit the patients daily in order to collect all the data related to the study. Also, the nurse will assess the potential development of any adverse event, and will collect all the information in the database. Adverse events will be classified according to their severity and causality. Only the serious adverse events, and those considered to be related to the use of the product of the study will be reported to the study promoter and to the regulatory authorities.

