### Statistical analysis

The analysis of the data will be carried out during the last 6 months of the project when all fieldwork has been completed. The database will then be analysed using the stepwise logistic regression model of the R software (R v. 3.2.5). The analyses will be made by intention-to-treat (all patients randomised who have a primary endpoint available). To handle missing data multiple imputation will be done under the missing at random assumption.

For the analysis of the primary endpoint, the frequency of colonisation of the CVC hubs in both treatment groups will be compared. For the analysis of the secondary endpoints, the frequency of CRBSI will be compared between the two groups, as well as the need for CVC removal for any cause and overall case-fatality rate (30 days). Exploratory subgroup analyses will be conducted by underlying haematological condition (leukaemia, autologous HSCT, and allogeneic HSCT) and by centre. Due to the fact that a patient could have been included twice, the potential impact of independence violation will be assessed repeating the main analysis using patient as a cluster.

The statistical analysis will be carried out using a Student’s *t* test and a chi-square test. A multivariate analysis will be performed to verify the absence of confusion by other variables. In addition, free time of colonisation of the catheter and BSI will be analysed using Kaplan-Meier curves, and they will be compared between both groups by means of the log-rank test (Mantel-Cox test). A value of *p* = 0.05 will be considered statistically significant.

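### The 30-day windows for death, CRBSI and catheter removal are anchored at an end of intervention that study outcomes themselves trigger, so the span observed from randomisation can differ by arm

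*Protocol article*

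**What the plan says.** All places are in the Methods of the protocol article.

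- **Stopping events** (Follow-up criteria and participant timeline): "Patients will continue to receive intervention until one of following events occurs". The list includes a positive hub culture, neutrophil recovery, catheter removal for any cause, CRBSI, an unavoidable continuous infusion, discharge and death.
- **Start of follow-up** (same section): "Once the patient concludes the study for any of the previous events, a 30-day follow-up will take place to assess possible complications". Of patients stopped for hub colonisation it adds that "they will continue to be followed-up to check whether they develop CRBSI".
- **Mortality** (Definitions): "the 30-day case-fatality rate will be defined as death by any cause within the 30 days following the end of the intervention". Secondary endpoints repeats the anchor: "all patients included in the study will be followed up for a total of 30 days after the end of the intervention".
- **CRBSI** (Secondary endpoints): "The development of CRBSI will be assessed during intervention and up to 30 days after the last intervention". Catheter removal has the same window. CRBSI is also to be presented per 1000 admission days.
- **Hub swabs** (Primary endpoint): "three times weekly (approximately every 48-72 h) thereafter for culture, until the end of the intervention".
- **Analysis** (Statistical analysis): the frequencies of CRBSI, removal for any cause and 30-day death are compared between groups, with the chi-square test among the named methods. In addition, "free time of colonisation of the catheter and BSI will be analysed using Kaplan-Meier curves", compared by log-rank test.

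No outcome window is fixed from randomisation.

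**The concern.** A randomised comparison is cleanest when time zero and length of observation cannot depend on what was allocated. Here the window closes 30 days after an event that the treatment is meant to delay or prevent. A patient whose hub becomes colonised stops early and starts the 30-day clock early; a patient kept free of colonisation goes on to recovery, discharge or another stop.

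Three things follow.

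1. CRBSI and removal are counted over a span from randomisation that is longer, on average, in the arm with less colonisation. A plain comparison of frequencies makes no allowance for this.
2. The windows open in different risk states: during neutropenia for a patient stopped by colonisation, at neutrophil recovery for many others. The Background itself names the neutropenic phase as the time of greatest catheter-infection risk.
3. Death is a stopping event, yet the mortality definition counts deaths after the end of the intervention. How a death during the intervention counts is unclear. The anchor is also worded in two ways, as the end of the intervention and as the last intervention. With locks every 48 to 72 hours these can differ by days.

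At stake is the cleanness of three secondary comparisons, not the primary endpoint.

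**Working it through.** The plan gives no figure for the length of the lock course or of observation, so there is none to reproduce. From the document come the 20% and 5% colonisation rates (Sample size) and the 30-day follow-up. Course length, death hazard and competing hazards below are assumptions.

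**1. A single patient.** Assume a 14-day course and colonisation, on average, half-way through. A colonised patient is observed 7 + 30 = 37 days from randomisation, any other 14 + 30 = 44 days. The difference is 7 days, or 7/44 = 16%.

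**2. Arm means, simple version.** Each colonised patient loses half a course. Control: 14 − 0.20 × 7 = 12.6 days of intervention. Taurolidine: 14 − 0.05 × 7 = 13.65 days. The gap is 0.15 × 7 = 1.05 days.

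**3. Arm means, constant colonisation hazard.** Let the natural end of the course D be gamma-distributed with shape 9 and mean m, and time to colonisation C exponential with rate h. The end of intervention is E = min(C, D). Setting P(C < D) = p gives h = (9/m)[(1 − p)^(−1/9) − 1], and then mean E = p/h. For m = 14 and p = 0.20: h = (9/14)(0.0251) = 0.01614, so mean E = 0.20/0.01614 = 12.4.

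| Mean course m (days) | Control: mean E + 30 | Taurolidine: mean E + 30 | Gap (days) |
|---|---|---|---|
| 10 | 38.9 | 39.7 | 0.9 |
| 14 | 42.4 | 43.6 | 1.2 |
| 21 | 48.6 | 50.4 | 1.8 |

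Only colonisation was modelled as an outcome-driven stop; CRBSI and removal were not added as separate stops.

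**4. Deaths with no true effect.** Assume a constant, equal death hazard giving 10% dead by day 30: λ = −ln(0.90)/30 = 0.00351 per day. For m = 14:
- Deaths from randomisation to E + 30 are about 1 − 0.90 × exp(−λ × mean E): 1 − 0.90 × exp(−0.00351 × 12.4) = 13.8% for control, and 14.2% for taurolidine with mean E = 13.6. Over all three course lengths, with 5% or 10% dead by day 30, simulation gave gaps of about 0.1 to 0.6 percentage points.
- Deaths strictly within the 30 days after E, the literal definition, are about 9.5% in both arms.
- Deaths by day 30 from randomisation are 10% in both arms by construction.

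**5. The colonisation curve.** Swabbing ends with the intervention, so CRBSI, removal or death ends observation for colonisation. With colonisation hazard h and competing hazard c, one minus Kaplan-Meier at day 21 is 1 − exp(−21h), and cumulative incidence is [h/(h + c)] × [1 − exp(−21(h + c))]. Take h = 0.0149 for controls.
- Kaplan-Meier: 1 − exp(−0.313) = 26.9%.
- c = 0.01 per day (assumed, for CRBSI, removal and death only): 0.598 × (1 − exp(−0.523)) = 24.4%.
- c = 0.06 per day (every stop treated as competing, including recovery and discharge): 0.199 × (1 − exp(−1.573)) = 15.8%.

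For taurolidine, h = 0.0034 gives 6.9% by Kaplan-Meier and 6.2% with c = 0.01.

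**The case against.** The strongest reply is that the consequence is negligible. A gap of one to two days in about 40 to 50, on secondary endpoints only, will not change a conclusion. It arises only if the lock works, and for CRBSI and removal it runs against the lock, so it is conservative. This stands as to size. It does not make an outcome-dependent time zero a good choice when an unaffected one is available from the same data.

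Two further replies hold in part. A CRBSI or removal that stops the intervention has already been counted as that endpoint, so colonisation is the main trigger for those two outcomes. The CRBSI rate per 1000 admission days allows somewhat for unequal time. But its numerator runs on after discharge, which is itself a stopping event, so admission days are not the days at risk.

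A reader might also infer several stronger points that the document does not support:
- **That treated patients get a longer mortality window.** Read literally, the definition gives everyone 30 days; what shifts is when those days begin.
- **That both Kaplan-Meier curves are cut at the end of intervention.** This follows only for colonisation, because swabbing stops there. For bloodstream infection, observation continues for 30 days, explicitly so after colonisation.
- **That Kaplan-Meier overstates control colonisation by 11 points (27% against 16%).** This needs neutrophil recovery and discharge to count as competing events. With only CRBSI, removal and death at an assumed 0.01 per day, the contrast is about 27% against 24%. The article states no censoring rule, and that detail may sit in an analysis plan not shown.

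**Conclusion.** The point holds as a cheap improvement, not as a serious bias. The document fixes the windows for death, CRBSI and catheter removal at an end of intervention that the primary endpoint, two secondary endpoints and death trigger, and it compares plain frequencies.

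If the lock performs as the sample-size section assumes, the control arm's span from randomisation is shorter by about 0.9 to 1.8 days on average for assumed mean courses of 10 to 21 days. For a colonised patient on an assumed 14-day course it is about 7 days shorter. The average bias is small and confined to secondary endpoints. For CRBSI and removal it leans against the lock. For mortality its direction is uncertain, because windows open in different risk states and the counting of deaths during the intervention is unclear.

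On the curves, what stands is limited: CRBSI, removal and death compete with observed colonisation, and the second curve is labelled BSI, whereas the declared endpoint is CRBSI and the abbreviation list separates the two.

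**What to change.** 1. Compare death, CRBSI and catheter removal for any cause (as the Statistical analysis section already words it) over one common window from randomisation, for example to day 30. Follow-up runs to the end of intervention plus 30 days, and the intervention cannot end before randomisation. Day 30 is therefore already covered for every patient not withdrawn or lost. All deaths from randomisation then count, including those during the intervention.
2. Keep the current end-of-intervention window as a secondary analysis, with one wording for its anchor and a stated rule for deaths during the intervention.
3. For colonisation, add cumulative incidence with CRBSI, removal and death as competing events, as a sensitivity analysis beside the planned Kaplan-Meier curve.
4. Make the second curve match the CRBSI endpoint.

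**Cost.** Wording and minor programming, with no new visits or data and no change to the rules for stopping the locks. Recruitment is described as still open and unblinding comes only after the trial concludes, so the change can be made blind. There is a small downside: some patients may still be receiving locks at day 30, and later events then appear only in the secondary window. For a gamma course length with shape 4 (an assumption), this is about 3% of patients at a mean of 14 days and 18% at 21 days.
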